### Interim analyses {21b}

There are no plans for interim analyses because the intervention presents a low risk. The trial will proceed as scheduled unless serious adverse events warrant early termination, in which case the principal investigator will decide in consultation with the ethics committee.

### Methods for additional analyses (e.g. subgroup analyses) {20b}

There are currently no plans to conduct subgroup analyses in this trial.

### Methods in analysis to handle protocol non-adherence and any statistical methods to handle missing data {20c}

All analyses will follow the intention-to-treat (ITT) principle. Missing data will be addressed using multiple imputation under the assumption of missing at random (MAR). Anthropometric measures, body composition variables, blood pressure, biochemical indices, and questionnaire scores will be included in the imputation model using a fully conditional specification (FCS) approach. In addition, sensitivity analyses will be performed with complete cases to confirm the robustness of the results.

### Plans to give access to the full protocol, participant level-data and statistical code {31c}

Our complete trial protocol will be published in a peer-reviewed journal. We will make anonymized participant-level data and statistical code available upon a reasonable request from the corresponding author, following our data sharing policies and after getting the necessary ethical approvals.

## Oversight and monitoring

### Composition of the coordinating centre and trial steering committee {5d}

In accordance with university regulations, one member of the reviewing panel (made up of independent experts in nutrition, biostatistics, and ethics who are not affiliated with the sponsor) from the university Ethical Committee is elected to assess the adherence to the research proposal and monitor the correctness of data analysis. According to university regulations, once 5% of the sample size data has been gathered, the inspector will evaluate the consistency between the proposal and the data collection and intervention processes. If any complications arise that disrupt the study or lead to serious side effects, the study will be stopped, and these issues will be reported to the Ethical Committee. Participants will be urged to inform the researcher of any adverse events experienced in connection with the intervention supplement. The researcher will then evaluate the reported adverse event alongside the research team, and should a connection between the supplement and the adverse event be established, it will be documented. If the adverse event becomes too intolerable for a participant, they will have the option to withdraw from the study.

### Composition of the data monitoring committee, its role and reporting structure {21a}

If additional assessment is necessary, a Data Monitoring Committee (DMC)—made up of the Ethical Committee members who reviewed the proposal, along with supplementary experts for specific evaluations—will be convened. The study inspector will provide reports to the Ethical Committee. Throughout the study, the inspector is permitted to perform random checks on the procedures without notifying the research team. The inspector will maintain no financial or conflicting interests with either the sponsor or the research groups involved. The committee has no financial or professional connection to the sponsor and will conduct unannounced audits to ensure the trial adheres to ethical and methodological standards.

### Adverse event reporting and harms {22}

Participants will stay in contact with the researchers once a week, and any issues or adverse effects that arise during the intervention will be discussed. If any adverse side effects or problems are identified, participants will be removed from the study after consulting with the research team and specialists in the relevant field. We follow institutional guidelines for reporting and managing adverse effects.

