### Exclusion criteria

We will exclude individuals who are pregnant, lactating, or postmenopausal; professional athletes or individuals undergoing changes in the intensity and frequency of their physical activities throughout the last month; individuals with a confirmed clinical history of eating disorders, gastrointestinal diseases, cardiovascular, hepatic, renal, pulmonary, or endocrine diseases (such as thyroid conditions or diabetes), cancer, or any severe acute or chronic disease; current smokers, drug or alcohol addicts; those with known allergies or sensitivities to supplement or placebo components; individuals with a history of bariatric surgery; those who skip at least one meal; individuals on special diets, such as vegetarian diets; those with a regular intake of more than 300 mg of caffeine or more than 30 g of fiber per day; those adhering to a calorie-restricted diet for three months prior to the start of the study; individuals who routinely consume pre-, pro-, and synbiotic products; those who take antibiotics for one month before the study begins; or individuals using medications, including cholesterol and lipid-lowering drugs (e.g., statins), blood sugar-lowering drugs (e.g., insulin, metformin, liraglutide), antihypertensive medications, drugs affecting GI function, weight, body composition, or appetite (e.g., antipsychotics, corticosteroids, anti-obesity drugs, oral contraceptives, antidepressants), weight loss supplements (including those affecting appetite, metabolism, or food absorption) such as orlistat, and drugs interacting with green tea (e.g., digoxin, tacrolimus, warfarin).

Participants will be excluded from further analysis if they opt out, use antibiotics or other pre-, pro-, and synbiotic products, or meet the exclusion criteria anytime during the study, or do not comply with their assigned treatment regimen during the study.

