### Criteria for discontinuing or modifying allocated interventions {11b}

For safety concerns, if a participant experiences severe or ongoing adverse effects (like unmanageable stomach symptoms or allergic reactions) due to the supplement, intervention will be stopped after discussing with a physician. The criteria for stopping or changing the assigned interventions include: (1) Safety concerns, such as severe adverse events (like anaphylaxis or severe gastrointestinal symptoms) or persistent intolerable reactions. (2) If a participant requests to stop at any time, their request will be *honored without consequence. (3) If a participant’s** condition worsens, requiring the intervention to be terminated.*

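### The harms section removes participants from the study for any adverse effect, against two other sections, and the exclusion criteria then drop leavers and non-compliers from an analysis declared intention-to-treat

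*Protocol article*

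**What the plan says.** Three sections of the protocol article say what happens to a participant with an adverse effect.

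- **Adverse event reporting and harms {22}:** "If any adverse side effects or problems are identified, participants will be removed from the study after consulting with the research team and specialists". It adds: "We follow institutional guidelines for reporting and managing adverse effects". Those guidelines are not shown.
- **Criteria for discontinuing or modifying allocated interventions {11b}:** "if a participant experiences severe or ongoing adverse effects" attributed to the supplement, the "intervention will be stopped after discussing with a physician". The listed criteria are safety (severe events or persistent intolerable reactions), the participant's request, and a worsening condition.
- **Composition of the coordinating centre and trial steering committee {5d}:** where an event is too intolerable for participants, "they will have the option to withdraw from the study". On recording, the team assesses each reported event and, "should a connection between the supplement and the adverse event be established, it will be documented".

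Two sections decide who is analysed.

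- **Exclusion criteria:** "Participants will be excluded from further analysis if they opt out, use antibiotics or other pre-, pro-, and synbiotic products". The same sentence extends to those who meet an exclusion criterion during the study or "do not comply with their assigned treatment regimen during the study".
- **Section {20c}:** all analyses follow intention-to-treat, with multiple imputation under missing at random (MAR) and a complete-case sensitivity analysis.

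**The concern.** Sections {11b} and {5d} can be followed together. Section {22} differs from both in its trigger (any effect or problem) and in its consequence (leaving the study, not stopping sachets). A coordinator who keeps a participant with mild bloating departs from {22}; one who removes that participant goes beyond {11b}. This has practical force, because section {23} has auditors check compliance and escalate deviations.

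No section says that someone who stops sachets stays in follow-up. Removal would probably end outcome collection for people who could still be measured at week 8. Correcting {22} alone would not be enough: a participant who stops sachets for tolerability can be classed as non-compliant and dropped under the Exclusion criteria. Tolerability may differ between an active mixture and microcrystalline cellulose, so the loss may depend on arm. That is the situation intention-to-treat is meant to protect against.

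A smaller issue concerns recording. Section {5d} promises documentation where a link with the supplement is established. If that judgement decided what is recorded, part of the between-arm comparison of events would be lost, and that comparison is better evidence on causation than case-by-case opinion.

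**Working it through.** **Step 1. Compare the rules on adverse effects.**

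| Section | Trigger | Consequence |
|---|---|---|
| {22} | Any adverse effect or problem, after consultation | Removed from the study |
| {11b} | Severe or ongoing effects; request; worsening | Intervention stopped |
| {5d} | Event intolerable to the participant | May choose to withdraw |

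The consultation in {22} could act as a filter, but the sentence names no criterion under which a participant stays. The conflict in wording remains.

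**Step 2. Compare the rules on analysis.** The Exclusion criteria take out those who opt out, use prohibited products, meet an exclusion criterion or do not comply. Section {20c} says every analysis is intention-to-treat. Both cannot hold for the same participant. The complete-case sensitivity analysis does not repair this, since it also leaves out people without a week-8 value.

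**Step 3. Compare the recording provisions.** Symptom logs {11c}, the Gastrointestinal Symptom Rating Scale (GSRS) at start, mid-point and end, and the severe-event procedure {17b} cover part of what {5d} might miss. What may go unrecorded is a non-severe, non-gastrointestinal event judged unrelated, and only if the institutional guidelines do not require it. A participant removed early would probably also miss later GSRS assessments.

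**Step 4. Illustrate the size.** The article gives no event rates and has no figure to reproduce on this point. It does give 36 per arm and a standardised effect of 0.80 (Sample size {14}). All other inputs below are assumptions.

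*Precision.* Let p be the share of each arm with no week-8 value, with only baseline data informing the imputation. The standard error rises by about 1/√(1 − p).

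| p | People per arm (36 × p) | Factor |
|---|---|---|
| 0.10 | 3.6 | 1/√0.90 = 1.05 |
| 0.20 | 7.2 | 1/√0.80 = 1.12 |
| 0.30 | 10.8 | 1/√0.70 = 1.20 |

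*Bias.* Let Δp be the between-arm difference in the share removed, and d the amount (in SD) by which removed people differ from their MAR prediction, taken as equal in both arms. The shift in the between-arm difference is Δp × d.

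| Δp | d = 0.25 | d = 0.50 |
|---|---|---|
| 0.05 | 0.0125 SD | 0.025 SD |
| 0.10 | 0.025 SD | 0.05 SD |
| 0.20 | 0.05 SD | 0.10 SD |

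Against 0.80, the ends are 0.0125/0.80 = 1.6% and 0.10/0.80 = 12.5%. The size of any recording gap cannot be estimated.

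**The case against.** The best counter-argument is that automatic removal for a mild effect cannot be the working rule. A 7-point symptom scale completed three times and monthly review of symptom logs presuppose that people with symptoms stay in. Section {11b} is where discontinuation criteria belong, and {22} is a short paragraph in a condensed article that makes removal follow specialist consultation. Loose drafting is a natural explanation. This stands as a reason for moderation: a reader might infer that every mild complaint ends participation and cancels the week-8 visit, but {22} does not say that measurement is cancelled, and the other sections point the other way. It does not reconcile the wording of {22} with {11b}.

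Second, a reader might infer from {5d} that unrelated events will not be recorded. The text says that related events will be documented; it does not say that others will not. Section {22} has weekly contact at which problems are discussed, and defers reporting to guidelines not shown. This objection largely stands, so the recording point is conditional and secondary. Blinded rating of relatedness is good practice in itself.

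Third, the clash between the Exclusion criteria and {20c} exists whatever {22} says. That is true, but it also determines whether correcting {22} would achieve anything, so the two need fixing together.

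Fourth, the size is wholly assumed. The upper end of the bias range needs a 20-point difference in removal (0.20 × 36, about 7 people) and a 0.50 SD departure from MAR; nothing in the article points to either, and it describes the intervention as low risk. Removals may also already sit within the planned 20% dropout, so they should not be added to it. All of this stands.

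**Conclusion.** The point holds as two conflicts in the text: {22} against {11b} and {5d} on what an adverse effect leads to, and the Exclusion criteria against {20c} on who is analysed. Both should be corrected, because following the rules as written could lose or drop post-randomisation data in a way that depends on arm.

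The claim goes no further than a risk. The documents do not show that bias has occurred or will occur. The calculated shift is modest and its direction unknown; it assumes the same departure from MAR in both arms and covers imputed values, not people excluded outright. The recording point holds only if the institutional guidelines do not already require all events to be recorded. Confidence is medium, since the consultation step and the symptom monitoring make the literal reading of {22} unlikely in practice.

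**What to change.** **(a) Section {22}.** Replace the removal sentence with: *Sachets are stopped on the criteria of section {11b}, or when a safety-relevant exclusion criterion arises (for example pregnancy, or starting a drug that interacts with green tea). Outcome assessments continue to week 8 unless the participant withdraws consent to further data collection.* The safety-relevant clause is needed so that (a) and (b) together still give a stopping rule for these participants.

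**(b) Exclusion criteria.** Replace the post-randomisation sentence with: *Opting out, non-compliance, stopping sachets, prohibited product use, or meeting an exclusion criterion after randomisation is recorded but does not exclude a participant from the intention-to-treat analysis; missing values are multiply imputed as in section {20c}.* Make this change before unblinding.

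**(c) Section {5d}, only if the institutional guidelines do not already require it.** State: *Every reported adverse event is recorded in both arms; relatedness is rated separately and does not decide whether the event is recorded.*

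**Cost and timing.** This is an amendment needing ethics committee approval (section {25}), some week-8 visits for people off sachets, and a longer event listing. The weekly contacts and monthly visits already exist. Recruitment began on June 22, 2025 and was expected to end on October 23, 2025, so (a) and (c) may reach only some participants. Change (b) applies to all of them.

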### Frequency and plans for auditing trial conduct {23}

The university’s clinical trial monitoring protocol mandates strict adherence to approved ethical and methodological standards, overseen by a three-member supervisory team specified in the research contract. These independent auditors from the ethics committee, with no association with the research team or sponsor, will conduct audits and perform unannounced random checks at least twice during the trial. Additionally, the sponsor will have no role in designing, executing, or interpreting audits. Investigators must notify the Research Administration when reaching 5% of the target sample size to coordinate field audits, which are scheduled on predetermined days, with the research team proposing two alternative times. During audits, the supervisory team evaluates compliance with protocols, including sampling methods, randomization, blinding, data integrity, informed consent documentation, and confidentiality measures. Investigators are responsible for ensuring staff availability to provide requested records and answer questions. Deviations from the approved protocol trigger a structured escalation process: initial non-compliance results in a corrective action period, followed by a re-audit. Persistent deviations may lead to referral to the Clinical Trials Committee and possible study termination by the Research Council. This process, overseen by the Vice Chancellor for Research and Technology, emphasizes transparency, accountability, and institutional oversight, with all audit results documented to maintain traceability and uphold research integrity.

### Plans for communicating important protocol amendments to relevant parties (e.g., trial participants, ethical committees) {25}

Any significant protocol changes will be submitted for approval to the Ethical Committee of Mashhad University of Medical Sciences before they are implemented. Approved amendments will be communicated to all investigators and documented in IRCT.

### Dissemination plans {31a}

The study results will be published in relevant publications. Access to the data will begin six months after the results are published. The non-identifiable personal information of the participants will then be available to other researchers at academic institutions upon request to the corresponding authors. It may only be used for research purposes. The trial results will also be updated on the IRCT.

## Discussion

Obesity and its related disorders present a significant public health challenge globally. In addition to traditional weight loss medications, next-generation probiotics (NGPs) appear to hold promise as a preventive and treatment measure against obesity [25]. Emerging research is investigating the benefits of next-generation probiotic supplements, with a focus on the effects of *Akkermansia muciniphila* on metabolic conditions such as obesity and diabetes.

Although *Akkermansia muciniphila* shows potential for treating obesity and type 2 diabetes (T2D), human research is scarce [26]. Further human studies could better clarify the preventive or therapeutic benefits of this promising next-generation probiotic.

Although studies have focused on the effectiveness of live or pasteurized *Akkermansia muciniphila,* the effect of this bacterium in combination with prebiotics has not yet been investigated. Filling this gap could result in innovative treatments for metabolic conditions, including obesity. The purpose of this study is to investigate the effect of a novel beverage containing pasteurized *Akkermansia muciniphila*, glucomannan, and green tea extract on body composition, anthropometric indices, metabolic markers, blood pressure, and appetite in adults with overweight or obesity. If the intervention shows favorable outcomes, it will represent a valuable step toward developing recombinant supplements with specific therapeutic targets.

## Trial status

The current protocol version is 4.0, dated September 5, 2025. Recruitment for the study began on June 22, 2025, and it is estimated that recruitment will be completed by October 23, 2025.

## Data Availability

Data from the main study will be available after obtaining institutional approval upon written request.

## Abbreviations

*A. muciniphila*: *Akkermansia muciniphila*
BP: Blood pressure
BMI: Body mass index
CKD: Chronic kidney disease
CVD: Cardiovascular diseases
DMC: Data Monitoring Committee
EGCG: Epigallocatechin-3-gallate
FBS: Fasting blood sugar
GSRS: Gastrointestinal Symptom Rating Scale
HDL: High-density lipoprotein
IRCT: Iranian Registry of Clinical Trials
KGM: Konjac Glucomannan
MET: Metabolic Equivalent of Task
NAFLD: Nonalcoholic fatty liver disease
NGPs: Next-generation probiotics
SPSS: Statistical Package for the Social Sciences
TC: Total cholesterol
LDL: Low-density lipoprotein
LDL-C: Low-density lipoprotein cholesterol
T2D: Type 2 diabetes
T2DM: Type 2 diabetes mellitus
VAS: Visual Analogue Scale
WHO: World Health Organization
MetS: Metabolic syndrome
